### Intervention

The two care pathways and associated research interventions are depicted graphically in Figure 2. All visits and telephone calls described below will be undertaken by clinical staff of the Community COPD Service team.

**Figure 2 F2:**
[figure not shown]
**CONSORT Flow Chart**.

#### Tele-health Intervention

Patients recruited to the Tele-health supported Community COPD Service will be taught how to use the technology to aid monitoring of their condition. The patient will be required to enter information into the tele-health equipment on a daily basis to monitor their condition. Data provided to the system will be recorded on the web server so patient compliance with using the equipment can be assessed. If the patient fails to enter information into the equipment for three continuous days the system generates an alert on the web server which is acted upon by the COPD team.

#### Usual Care Group

Patients recruited to the standard Community COPD Service will not receive the technology but will have six visits with specialist COPD clinicians from the Community COPD Service as described in Figure 2.

### Data collection tools

#### St. Georges Respiratory Questionnaire

Patients will be asked to complete the St. Georges Respiratory Questionnaire score upon admission to either the Tele-health supported or standard Community COPD Service, on discharge from the service and six months after discharge from the service. This questionnaire is a validated and widely-used instrument which measures health impairment in patients with COPD on a scale of 0 to 100 (greatest impairment). This scale is responsive to change with a minimum important difference (MID) of 4.

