**Methods/Design:**

We describe a pilot study for a two arm, one site randomized controlled trial (RCT) to determine the effect of tele-health monitoring on self-management, quality of life and patient satisfaction. Sixty patients who have been discharged from one acute trust with a primary diagnosis of COPD and who have agreed to receive community clinical support following discharge from acute care will be randomly assigned to one of two groups: (a) Tele-health supported Community COPD Service; or (b) Usual Care. The tele-health supported service involves the patient receiving two home visits with a specialist COPD clinician (nurse or physiotherapist) then participating in daily tele-monitoring over an eight week period. Usual care consists of six home visits to the patient by specialist COPD clinicians again over eight successive weeks. Health status and quality of life data for all participants will be measured at baseline, on discharge from the service and at six months post discharge from the service.

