### Primary and Secondary Outcome Measures for the Definitive Trial

Two primary outcomes will be measured:

1. The health service primary outcome will be the proportion of patients who are re-admitted to hospital with COPD as the primary or secondary cause of their admission, either during, or six months following their discharge from the Tele-health supported or standard Community COPD Service. This will be assessed through analysis of patient-completed self-reporting diaries, which will be completed both during and for six months following the Tele-health supported or standard Community COPD Service and analysis of hospital admission data.

2. The patient-centred primary outcome will be changes in self-reported health status and quality of life as measured by comparison of the patients' St. Georges Respiratory Questionnaire score upon admission to either the Tele-health supported or standard Community COPD Service, on discharge from the service and six months after discharge from the service.

There are four secondary outcomes:

1. Proportion of patients requiring unscheduled health care support to manage their COPD (including A&E, GP or community nurse visits) either during or six months following the standard Community COPD Service. This will be collected using a paper format self-reporting diary for the standard Community COPD Service and via the monitoring system for the Tele-health supported service; and analysis of hospital, GP and community nursing activity data.

2. Cost effectiveness of intervention. Costs and outcomes will be collected for each individual patient recruited to the pilot trial. The data to be collected for cost estimates will focus on usage of emergency and home-based care by participants. Health related quality of life will be measured using the EuroQol 5 Dimensions questionnaire (EQ-5D), which can be combined with mortality data to produce quality adjusted life years (QALYs). The EQ-5 D is a simple patient completed questionnaire (typically taking less than five minutes to complete), and has been incorporated into the COPD self-completed patient diaries. To ensure monthly data collection it has been embedded into the diaries collected during weeks 1 and 5, whilst the patient is enrolled on the Community COPD Service (both modalities) and subsequent diaries completed each month following discharge from the Community COPD Service.

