**Figure 1 F1:**
[figure not shown]
**Graphical depiction of the interventions**.

Whilst still in hospital, either the COPD or ward staff (depending upon the referral route) will provide the patient with a leaflet about the Community COPD Service, a patient information sheet and a copy of the research consent form prior to their discharge. The patient will be made aware that the clinicians from the Community COPD Service will provide them with more information about the research on their first visit (day after patient's discharge from the hospital). On this first home visit, a clinician from the Community COPD Service, who has undertaken Good Clinical Practice training and is therefore qualified to seek patient consent to participate in the trial, will confirm that patients meet all the inclusion criteria to participate in the trial; will explain the study if any additional information is requested; and seek consent to participate in the trial. They will then aim to recruit patients initially to the service and, secondly, to the trial. Should a patient not wish to participate in the research they can still receive the standard Community COPD Service but will not be included in the study. As identified in the exclusion criteria, any patient unwilling to consider the technology as part of their care plan will be excluded from the trial although they can receive the standard Community COPD Service.

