### Randomisation

Consented patients will be randomized using a web-based system developed by the University of Sheffield Clinical Trials Research Unit. A simple randomisation sequence will be used to allocate patients to either the standard Community COPD Service or the Tele-health supported Community COPD Service. It is impossible to blind patients or clinical staff to the trial arm, but research staff will be blind to the allocation. Administration staff at the Community COPD Service will use the web-system to identify the allocation for the next patient who consents to participate in the trial, but at this stage the clinician seeking consent from the patients will be blinded to the allocation to prevent any bias in recruitment. Once consent has been received, the clinician will contact the administration centre to obtain the allocation. At this point they will inform the patient of the allocation and tell them whether they will receive the tele-health supported or standard community COPD service.

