## Discussion

The high local prevalence of COPD contributed to the £2.2 million cost of related admissions billed to the local health service between April 2006 and March 2007 [16]. Consequently, the acute trust, the Commissioners and PCT have all recognized the urgent need to support patients and minimize unnecessary hospital admissions and emergency room visits. This initiative is one of the approaches being considered to address this goal.

Whilst the need to improve care delivery modalities and reduce reliance on the acute sector is recognized, in reality, the shift to the primary sector is proving more difficult to enact than initially anticipated. This project is posing a number of challenges for the PCT undertaking the implementation of the tele-health supported Community COPD Service.

In developing their project plan for implementation of the tele-health supported service, the PCT realized that they did not have the resources and expertise to undertake the installation of equipment into patient's homes. Within the city, the Local Authority had established a service providing a 24-hour, 365 day a year emergency response service for approximately 7,000 residents of the Borough, with approximately 4,700 service users linked to the service using Individual Alarm Units and the remainder in Local Authority and Housing Association accommodation linked by hard-wired intercom systems. Clearly this centre had experience in installing comparable technology into people's homes, so the PCT created a partnership with the Local Authority, tasking them with the installation of the tele-health equipment within 72 hours of hospital discharge.

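### The baseline SGRQ is not placed before the arm is disclosed, and the first stated EQ-5D falls after disclosure and by a different mode in each arm

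*Protocol article*

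**What the plan says.** **SGRQ.** The section on the questionnaire states: "Patients will be asked to complete the St. Georges Respiratory Questionnaire score upon admission to either the Tele-health supported or standard Community COPD Service". It is repeated at discharge from the service and six months later, and a minimum important difference (MID) of 4 points is given. The outcomes section uses the same timing and makes the score a primary outcome of the definitive trial: "The patient-centred primary outcome will be changes in self-reported health status and quality of life". The abstract says only that health status and quality of life "will be measured at baseline, on discharge from the service and at six months post discharge from the service".

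**First home visit.** The text after Figure 1 puts this visit on the day after hospital discharge. The clinician confirms eligibility, seeks consent and aims to "recruit patients initially to the service and, secondly, to the trial". Under Randomisation, the clinician contacts the administration centre for the allocation once consent is given, and then: "At this point they will inform the patient of the allocation". The same section accepts that neither patients nor clinicians can be blinded.

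**EQ-5D.** The cost-effectiveness paragraph says of this instrument that "it has been embedded into the diaries collected during weeks 1 and 5", in both forms of the service, and then into monthly diaries after discharge from the service. The Diaries section has tele-health patients answer the same questions through the technology. The Discussion describes the Local Authority's part as "tasking them with the installation of the tele-health equipment within 72 hours of hospital discharge".

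**The concern.** A baseline used to measure change should be recorded before the patient knows the arm. Here the patient learns it during the first visit, and the text does not require the SGRQ to come before that moment. Both instruments are self-reports. A patient who has just been told that equipment will be installed, or that it will not, may answer differently for that reason alone. If so, the reference point for a primary outcome carries part of the arm difference.

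For the EQ-5D the stated schedule contains no value from before allocation. The QALY comparison then has no clean utility covariate for chance differences between arms. This matters in the pilot, which uses simple randomisation with 60 patients. It also matters beyond the pilot, because the pilot tests the definitive trial's methods and the definitive trial is to follow immediately if no issues arise.

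**Working it through.** No figure in the document bears on this point, so there is none to reproduce. The check is of the order of events, followed by an illustration on assumed values.

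**1. SGRQ order.** The Randomisation section gives consent, then the call for the allocation, then disclosure. The SGRQ is timed "upon admission to either the Tele-health supported or standard Community COPD Service". Two readings are possible:

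- Admission means entry to the arm-specific service. The patient then already knows the arm. This is the more natural reading, since the wording names the two arms.
- Admission means entry to the Community COPD Service in general, which the text after Figure 1 places ahead of recruitment to the trial. The SGRQ could then come before the call.

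The text decides for neither. What is established is that it does not fix the SGRQ before disclosure.

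**2. EQ-5D order.** Disclosure is at the first visit, the day after discharge. The first stated EQ-5D is in a diary that belongs to the period on the service. For tele-health patients it is answered on equipment that may be installed up to 72 hours after discharge; for usual care it is in a patient diary, described as paper in the outcomes section. The first value therefore follows disclosure, and its mode, and possibly its day, differ by arm.

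**3. Effect on SGRQ.** Let *d* be the between-arm shift in baseline caused by knowing the arm. The difference in change is (difference at follow-up) − (difference at baseline), so the bias has size *d*. With baseline adjustment and slope β it has size β × *d*. Assumed: *d* = 0, 1, 2 or 4 and β = 0.5 to 0.7.

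| *d* (assumed) | Change score | Share of MID of 4 | Baseline-adjusted | Follow-up only |
|---|---|---|---|---|
| 0 | 0 | 0% | 0 | 0 |
| 1 | 1 | 25% | 0.5 to 0.7 | 0 |
| 2 | 2 | 50% | 1.0 to 1.4 | 0 |
| 4 | 4 | 100% | 2.0 to 2.8 | 0 |

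**4. Effect on QALYs.** Let *s* be a shift in the week-1 EQ-5D only, and take follow-up as about 34 weeks (8 on the service plus about 26).

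- Unadjusted area by the trapezoid rule, weeks 1 to 5: *s* × (4/2)/52. If the week-1 value is carried back to day 0: *s* × (1 + 4/2)/52.
- Adjusted for the week-1 value, with correlation *r* = 0.5 to 0.7: about *r* × *s* × 34/52, in the opposite direction and before netting off the small direct term above.

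| *s* (assumed) | Unadjusted QALYs | Adjusted for week-1 value |
|---|---|---|
| 0.02 | 0.0008 to 0.0012 | 0.007 to 0.009 |
| 0.05 | 0.0019 to 0.0029 | 0.016 to 0.023 |
| 0.10 | 0.0038 to 0.0058 | 0.033 to 0.046 |

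**5. Chance imbalance in the pilot.** With about 30 per arm and an assumed EQ-5D SD of 0.2 to 0.3, the standard error of a true baseline difference is SD × √(2/30) = 0.2 × 0.258 to 0.3 × 0.258, or about 0.05 to 0.08. By the formula in step 4, a chance imbalance of 0.05 would be expected to move the unadjusted QALY difference by 0.05 × 0.5 × 34/52 to 0.05 × 0.7 × 34/52, or 0.016 to 0.023. A pre-allocation EQ-5D would allow this to be adjusted for.

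**The case against.** The strongest reply is that the SGRQ half is an inference. The wording about admission may simply cover both arms in one phrase. The abstract calls the measurement baseline, recruitment to the service precedes recruitment to the trial, and Figure 2, which is said to show the research steps, is not available. An article may also leave the order of steps within a visit to the full protocol. This stands: a reader might infer that the SGRQ is definitely taken after patients know their arm, and the document does not support that.

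It is also fair that the size of any shift is assumed. Nothing in the document says that learning the arm moves the score, by how much or in which direction, and zero is possible. The arithmetic shows how a shift would be transmitted, not that there is one. The estimator is not fixed here and may be in an analysis plan that is not shown.

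A reader might further infer that QALYs are biased for want of a baseline EQ-5D. They are not: randomisation protects an unadjusted comparison, chance imbalance is a matter of precision, and other covariates such as age and prior admissions remain available. Finally, the figure of about 30 per arm belongs to the pilot, while the SGRQ primary outcome belongs to the definitive trial, whose size is not set.

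What the reply does not remove is the stated EQ-5D schedule, which has no pre-allocation value and differs in mode by arm, or the lack of any statement that the SGRQ precedes disclosure although the primary outcome is a change from it.

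**Conclusion.** The point holds in a limited form. The EQ-5D part is settled by the text as given: the first stated value follows disclosure and is collected differently in the two arms, so there is no pre-randomisation utility value for adjusting QALYs. For the SGRQ, the protocol leaves open whether the baseline precedes disclosure, and its wording leans towards after.

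The consequence depends on the analysis. A post-disclosure shift would pass in full into a change score and by roughly half to 0.7 of its size into a baseline-adjusted estimate, on the assumed slopes. Follow-up scores compared without a baseline term would not be affected by it, and unadjusted QALYs would move by under 0.006 even for an assumed EQ-5D shift of 0.10. The actual shift is unknown. The case for acting rests on how cheaply the ambiguity can be removed for a self-reported primary outcome in unblinded patients, not on a demonstrated bias.

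**What to change.** State the order at the first home visit: written consent; then the SGRQ and one EQ-5D, completed by the patient on paper in both arms; then the clinician's call to the administration centre for the allocation. Keep the week-1, week-5 and monthly EQ-5D diaries as planned. Name the pre-allocation SGRQ as the reference for SGRQ change and the pre-allocation EQ-5D as the covariate for QALYs. If the SGRQ is already meant to be completed before the call, one sentence saying so settles that half.

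The cost is a slightly longer first visit and one extra form; the protocol puts the EQ-5D at typically under five minutes. Sample size, care pathways and the web randomisation system need no change.

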#### Diaries

Patients recruited to the Usual Care Group will track their use of health services to assist in the management of their COPD by means of a self-reported questionnaire whilst on the eight week programme and for the subsequent six months. Patients will record whether they have contacted a health service provider because they had concerns about their COPD, who they contacted, why they contacted them and what happened as a result (telephone consultation, visit). The diaries will also be used to capture EQ5 D information on problems with mobility, self-care, usual activities, pain/discomfort and anxiety/depression.

Patients on the Tele-health supported Community COPD Service will be asked to answer the same questions as part of their routine use of the technology.

#### Tele-health service questionnaire

Patients on the Tele-health supported Community COPD Service will be asked to complete a questionnaire on discharge from the service. The questionnaire will ascertain their opinions about the technology, the installation process, training, use of the equipment, availability of support and removal of the equipment from their home.

### Research Governance

The trial will be conducted in accordance with MRC Guidelines [22,23]. The acute trust will act as the sponsor of this project.

A Trial Management Committee will be established and will consist of the Principal Investigator, Research Project Manager, research staff, PCT Operations Manager, Operational Project Manager and the clinicians. Meetings of this team will be held monthly during the three month pilot.

A Data Monitoring Committee will meet towards the end of the pilot to review adherence to enrolment, randomisation strategy and examine the trial data. This committee will consist of an independent statistician, an independent trialist, the Principal Investigator and Research Project Manager.

### Patient and Public Involvement (PPI)

In the acute trust, a local group founded on the principles of INVOLVE [24], known as the Consumers Research Advisory Group (CRAG), meet three to four times per year, and their key role is undertaking reviews of proposed projects. This generally involves reading research proposals, and other project literature, and providing feedback on any areas which the researcher has requested, or those the group feel are in need of revision or clarification. A copy of the protocol for this pilot has been shared with CRAG and will be discussed at their next meeting. Feedback from the group will be incorporated into the design and conduct of the subsequent research phases. The protocol for the definitive trial will again be shared with this group as will the findings of the research.

## Discussion

The high local prevalence of COPD contributed to the £2.2 million cost of related admissions billed to the local health service between April 2006 and March 2007 [16]. Consequently, the acute trust, the Commissioners and PCT have all recognized the urgent need to support patients and minimize unnecessary hospital admissions and emergency room visits. This initiative is one of the approaches being considered to address this goal.

Whilst the need to improve care delivery modalities and reduce reliance on the acute sector is recognized, in reality, the shift to the primary sector is proving more difficult to enact than initially anticipated. This project is posing a number of challenges for the PCT undertaking the implementation of the tele-health supported Community COPD Service.

In developing their project plan for implementation of the tele-health supported service, the PCT realized that they did not have the resources and expertise to undertake the installation of equipment into patient's homes. Within the city, the Local Authority had established a service providing a 24-hour, 365 day a year emergency response service for approximately 7,000 residents of the Borough, with approximately 4,700 service users linked to the service using Individual Alarm Units and the remainder in Local Authority and Housing Association accommodation linked by hard-wired intercom systems. Clearly this centre had experience in installing comparable technology into people's homes, so the PCT created a partnership with the Local Authority, tasking them with the installation of the tele-health equipment within 72 hours of hospital discharge.

This horizontal integration is an innovative model which has needed detailed planning and a great deal of collaboration. Both partners have provided extensive support to the project, developing detailed flowcharts to identify key activities, responsibilities and timings to ensure all elements of the project remain on track; developing training materials for staff and patients; shared forms to capture data required by all partners and shared spreadsheets to track patient-specific data to ensure there are no gaps in service delivery and technology-related data to ensure that its location and condition (installed and in use/in stock/unavailable - awaiting cleaning) are always known. Methods to address requirements for routine portable appliance (PAT) testing to meet the Electricity at Work Regulations [25], infection control, confidentiality of patient records and the safe installation of the technology have all needed to be addressed.

Tele-health may offer a way to provide care and encourage self-management of the condition for early stage COPD patients within the primary care sector, and this will be evaluated in the planned RCT. However, preparation for this RCT has provided evidence of specific challenges in implementing tele-health supported services which may require quite innovative solutions.
